### Cost-effectiveness analysis

Using the technique of cost-utility analysis (CUA), costs and patient outcomes will be compared between the doxapram and placebo arm. The time horizon will be the 18 to 24 months follow-up period of the trial. Both medical and non-medical costs will be analysed, following recommended methods for economic evaluations and costing studies in healthcare [40, 41]. Medical costs will include both costs during hospital admission and costs after hospital discharge (e.g., costs of visits to the outpatient department, physical therapy, speech therapy, visual and hearing aids). Resource consumption for all these items will be derived from electronic databases and from questionnaires, based on the Medical Consumption Questionnaire of the Institute for Medical Technology Assessment [42]. Non-medical costs related to severe disability, including costs of social care/day care, grade retention, and special education, will be calculated.

Regarding the patient outcomes, the CUA will look at survival, severe disability (as defined above), and HRQoL. HRQoL will be measured using the Child Health Utility 9D (CHU9D) instrument [43, 44]. Based on data on survival and responses to the CHU9D, quality-adjusted life years (QALYs) will be calculated. Finally, incremental cost-effectiveness ratios (ICERs) will be calculated, expressed as incremental costs per additional survivor without severe disability at 18 to 24 months corrected age and incremental costs per QALY gained.

#### Currently planned sub-studies

For all sub-studies, the blinding of the patients for the study team and researchers will be maintained during the project.

### Vital sign data analyses

Some of the participating centres will collect continuous high frequency monitor data that will be used to analyse the oxygenation in infants receiving either placebo or doxapram. Data on oxygen saturation (SpO_2_), heart rate and respiratory rate will be extracted from bedside monitors where possible. These measurements are part of the standard of care and will be performed without additional burden for participating infants. The vital sign data will be used to investigate the response to doxapram therapy compared to placebo, to identify responders and non-responders to doxapram therapy, and to explore the possibilities of real-time therapy evaluation.

### Neuromonitoring

The impact of doxapram on cerebral oxygenation, cerebral autoregulatory capacity (CAR), cerebral activity and neurological function will be investigated in some of the participating centres. Data collection on brain oxygenation, measured by Near Infra-Red Spectroscopy, includes regional cerebral oxygen saturation (rScO2), cerebral fractional tissue oxygen extraction (cFTOE) and transfer function (TF) gain. Cerebral activity will be assessed by multichannel video-EEG or aEEG. In addition, the neurological function will be assessed using the General Movement Assessment (GMA).

### Pharmacokinetic analysis

We aim to validate the previously reported population pharmacokinetic model of intravenously and gastro-enterally administered doxapram, and its active metabolite keto-doxapram, in preterm infants [26]. Plasma concentrations of doxapram and keto-doxapram will be quantified using an UPLC-MS/MS assay [45]. For this purpose, scavenged samples will be used and/or additional blood samples will be collected during routine blood sampling with a maximum of three samples of 0.1 ml per patient. The plasma concentrations will be quantified in some of the participants (*N*=50) from two participating centres. Because only half of these patients will receive doxapram we will also evaluate the caffeine levels (used as a standard administration in all patients). Caffeine exposure will be compared between the two treatment groups.

### Further sub-studies

Ideas for further sub-studies or analyses are welcome and will be discussed within the steering committee for costs, feasibility and scientific value.

## Ethics and dissemination

The study will be conducted according to the principles of the Declaration of Helsinki [46] and to the Dutch Medical Research Involving Human Subjects Act (WMO) and the Belgian and Canadian Law on patients’ right. Prior to randomization, written informed consent will be obtained according to the national guidelines from both, or at least one of the parents (not allowed in the Netherlands) or legal representatives. The informed consent form is added to the supplements, the additional participant information materials are available from the corresponding author on request. The local study team will provide information on the study for parents or legal representatives of preterm infants born before 29 weeks of GA who may develop an indication for doxapram therapy as soon as possible to allow for sufficient time to consider participation. Extended informed consent will be obtained in the subset of participants for specific sub-studies. The study is approved by the medical ethics committee of the Erasmus University Medical Centre (MEC-2020-0078), the Ethics Committee Research UZ/KU Leuven (S63834) and Health Canada (255525). All substantial amendments to the protocol will be notified to the medical ethics committees and all relevant parties once approval is acquired. Participants can leave the study at any time with no obligation to disclose a reason and without any consequences. The investigator can decide to withdraw a patient from the study for urgent medical reasons. Patients who are withdrawn from the study will be treated according to the standard of care guidelines. As long as parents provide consent, all patients will be followed up including neurodevelopmental outcome assessment in the outpatient clinic. The study sponsors, with the Erasmus University Medical Center as main sponsor for The Netherlands and Belgium and MICYRN (Mother Infant Child Youth Research Network) as sub-sponsor for Canada, have insurances that provide cover for damage to research participants through injury or death caused by the study.

## Data collection and management

Patient data will be collected by the local study team and stored in an electronic database (Castor EDC, Cewit B.V.) according to Good Clinical Practice guidelines. Security is guaranteed with login names, login codes and encrypted data transfer. An experienced data manager will check the database for completeness, consistency and plausibility. The saved data will be coded, and only the local principal investigator, the study team and the monitor have access to the source data. An independent monitor will review the study procedures in each participating centre.

## Dissemination

The study results will be submitted for publication in a peer-reviewed journal and presented at international conferences.

## Oversight and monitoring

An independent Data Safety Monitoring Board (DSMB), including experienced neonatologists, a pharmacologist and a statistician, will monitor the study on safety aspects and will provide recommendations regarding continuing or stopping the trial when 20, 50 and 75% of the anticipated outcome data are available. If the DSMB recommends modification or cessation of the study protocol, this will be discussed with a Trial Steering Committee, who will make the decision. The Trial Steering Committee includes experienced neonatologists as well as network and department directors who will monitor and supervise the progress of the trial. A patient involvement group, Create4Care, supports the trial and has an advisory role in the study. The patient group was involved from the start of the study and can support decisions on modification or cessation of the study protocol.

## Safety reporting

All adverse events reported by the parents of the participant, the investigator or the medical team will be recorded, according to the severity scale of Salaets et al. [32] with a distinction between suspected adverse events, unexpected suspected adverse events and context-specific adverse events. This study population (critically ill preterm infants) has a high risk of serious complications (so-called ‘context-specific serious adverse events (SAEs)’), which are inherent to their vulnerable condition and unrelated to the intervention studied here. These complications are included as primary and secondary outcomes of this study and are recorded in the Case Report Form. This documentation will include the date of diagnosis before or after randomization, classification/grading of the complication and type of action taken (if any). Since these complications are highly interrelated and of longitudinal character, it is impossible to indicate an exact date for the resolution or stabilization of each specific complication. Therefore, we will use the date of discharge from the NICU as the ‘end date’ of the complication.

Suspected unexpected serious adverse reactions (SUSARs) and SAEs will be reported to the sponsor by the local principal investigator within 48 h. The sponsor will report all SUSARs and SAEs (in the Netherlands) to the medical ethical committee of the Erasmus University Medical Centre and to the Central Committee on Research Involving Human Subjects. SUSARs will also be reported to Eudravigilance databank and to the Medicines Evaluation Board [47], and an overview of the SUSARs will be submitted every half year to the medical ethical committee. A safety report including all SUSARs and SAEs will be provided to the medical ethics committee and central committee and Health Canada annually. Parents of participating patients will be asked to report readmissions or other potential SAEs between hospital discharge and 18 to 24 months corrected age.

A special alert procedure will be used in case of the occurrence of a SUSAR (death during administration of the study medication) and NEC with a Bell stage of two or higher during or within 48 h after study medication cessation. These events will be brought directly to the attention of the principal investigator. If necessary, the Steering Committee will alert the DSMB, and the Steering Committee will provide a summary report after every ten alerts to the DSMB.

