Therapy is continued until the number and duration of the apnoea decrease below the estimated intervention threshold, or until respiratory failure occurs and invasive mechanical ventilation is needed according to the discretion of the attending physician (Figs. 1 and 2). Physicians are allowed to shortly interrupt the continuous administration of study medication in order to administer other (incompatible) medication intravenously. If the study medication is paused for less than 2 h, no additional action is necessary. An additional half-loading dose of the study medication should be administered if the interruption lasts between 2 and 4 h and a standard loading dose if the pause lasts longer than 4 h.

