### Adverse drug reactions

Adverse drug reactions will be monitored and registered during therapy. For severe events, we refer to the paragraph on safety reporting. Adverse drug reactions will include potassium levels, discomfort or irritability, the occurrence of tachycardia, hypertension, prevalence of convulsions and NEC. Both causality and severity will be evaluated for the possible adverse drug reactions. Causality will be assessed according to Kramer’s algorithm, which can be used to differentiate between possible and probable side effects [31]. The severity of all possible and probable adverse events will be assessed according to the INC Neonatal Adverse Events Scale [32].

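### The special alert covers death only while study drug is running, although NEC is covered for 48 h after cessation and therapy ends when ventilation is needed

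*Protocol article*

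**What the plan says.** The last paragraph of Safety reporting in the protocol article names two triggers for the special alert: "a SUSAR (death during administration of the study medication) and NEC with a Bell stage of two or higher during or within 48 h". The first trigger, death, is confined to what stands in the parenthesis. The second reads in full "NEC with a Bell stage of two or higher during or within 48 h after study medication cessation". Alerted events go straight to the principal investigator. The Steering Committee alerts the DSMB if it sees a need, and sends it a summary after every ten alerts.

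The Pharmacological intervention section says when therapy ends: when apnoea falls below the intervention threshold, "or until respiratory failure occurs and invasive mechanical ventilation is needed according to the discretion of the attending physician". The Study participants section also lets the attending team discontinue study medication whenever it judges this necessary, although it discourages doing so.

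Two other routes bear on deaths. SUSARs and SAEs go from the local investigator to the sponsor within 48 h, and from there to ethics committees and authorities. Under Interim analysis and stopping rules, neonatal mortality is compared by arm after 80, 200 and 300 inclusions.

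**The concern.** The alert is meant to bring events close to treatment to attention quickly, without waiting for an interim look. Its death trigger ends at the moment the drug stops, and the treatment rule stops the drug at the moment an infant becomes seriously unwell. The two rules together take out of the alert a group of deaths that it would be expected to catch: those that follow deterioration on study drug but occur after it has been withdrawn. The article gives no reason why NEC should have a tail after cessation and death should not.

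At stake is how soon a cluster of such deaths would be seen as a cluster. They would not go to the principal investigator as alerts, and they would neither count towards the ten alerts that prompt a DSMB summary nor appear in that summary.

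**Working it through.** No stated figure is in dispute, so the main check sets the rules side by side.

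| Event | Time | Special alert? | Source |
|---|---|---|---|
| NEC, Bell stage two or higher | on study drug | yes | Safety reporting |
| NEC, Bell stage two or higher | 47 h after cessation | yes | Safety reporting |
| Death | on study drug | yes | Safety reporting |
| Death | 3 h after cessation | no | Safety reporting |

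**Sequence.** (1) An infant on study drug goes into respiratory failure. (2) Invasive ventilation is judged necessary. (3) Therapy ends under Pharmacological intervention. (4) The infant dies. Step 3 comes before step 4, so the death does not occur during administration and the trigger is not met.

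**How many deaths?** Deaths missed = D × f, where D is the total number of deaths and f is the share that follow deterioration on drug but occur after cessation. The article gives neither. If overall mortality is assumed to be 5% to 15%, D is 0.05 × 396 = 19.8 to 0.15 × 396 = 59.4, about 20 to 59. Nothing in the article bounds f, which could lie anywhere from 0 to 1.

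**Does the interim comparison replace the alert?** It is not restricted to deaths on drug, so it does count these infants. The looks come after 80, then 200 − 80 = 120, then 300 − 200 = 100 further inclusions, with 396 − 300 = 96 after the last. Inclusion stops if the absolute difference is at least 10 points and the two-sided Fisher p-value is below 0.05. Assuming equal arms and some illustrative death counts in the lower arm, the smallest count in the other arm that meets both conditions is:

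| Inclusions (per arm) | Deaths | Difference | Fisher p |
|---|---|---|---|
| 80 (40) | 2 vs 9 | 7/40 = 17.5 points | 0.0476 |
| 80 (40) | 4 vs 12 | 8/40 = 20 points | 0.0482 |
| 80 (40) | 6 vs 15 | 9/40 = 22.5 points | 0.0406 |
| 200 (100) | 5 vs 15 | 10/100 = 10 points | 0.0317 |
| 200 (100) | 10 vs 21 | 11/100 = 11 points | 0.0494 |
| 300 (150) | 15 vs 30 | 15/150 = 10 points | 0.0228 |

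At the first look the rule responds only to a large imbalance. It is a periodic formal test and does not do the work of a prompt alert.

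**The case against.** The strongest case against the point is that the alert is an extra tier above ordinary SAE reporting. In a population where serious complications are expected, reserving that tier for deaths while the drug is running is a coherent choice. SAE reporting within 48 h has no stated on-treatment limit, the mortality comparison counts every neonatal death whatever the drug status, and death is part of the primary outcome. The article also condenses a full protocol that may define the alert more closely.

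Much of this stands: the deaths are captured. It does not remove the mismatch. The windows are stated, not omitted, and they differ within one sentence. SAE reports go to the sponsor, ethics committees and authorities, and the article describes no step from there to the DSMB between looks. If the 48 h tail was meant for both triggers, the sentence still needs correcting, because its parenthesis confines death to administration.

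Four stronger readings are tempting and are not supported:

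- **That most deaths escape the alert.** No mortality or timing is given, and some infants may die after therapy ended because apnoea had resolved.
- **That adverse reactions are registered only on treatment.** The article says "Adverse drug reactions will be monitored and registered during therapy" but does not make this exclusive. It continues "For severe events, we refer to the paragraph on safety reporting", and that section records all reported adverse events with no time limit. Clinical seizures and NEC are also secondary outcomes to hospital discharge.
- **That adverse-reaction counts are biased low in the doxapram arm.** A reaction that causes stopping begins before stopping, so it falls within therapy, and the same window applies to both blinded arms.
- **That the active metabolite named in the pharmacokinetic section justifies a particular window.** No half-life or clearance is given.

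**Conclusion.** The point holds for the death trigger of the special alert. A death that follows deterioration on study drug but occurs after cessation raises no special alert and does not enter the ten-alert summaries to the DSMB. This follows directly from the wording of Safety reporting and Pharmacological intervention. It rests on two readings, both the natural ones: that the 48 h tail attaches to NEC only, and that study drug has stopped once invasive ventilation is started for respiratory failure.

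The number of deaths affected cannot be derived from the article. The consequence is slower escalation between interim looks. It is not a loss of mortality data, and it does not affect the validity of the primary analysis. The change is still worth making, because it is cheap and concerns patient safety in a trial whose Discussion concedes that efficacy and safety are not yet established.

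**What to change.** In Safety reporting, extend the death trigger to the window the article already uses for NEC: during study medication or within 48 h after its cessation. State that cessation because of intubation is included, and reconcile the wording with the end-of-therapy rule in Pharmacological intervention. This changes reporting only and leaves treatment decisions as they are.

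The cost is one amended sentence and somewhat more alerts, so ten-alert summaries may fall due more often. The NEC trigger cannot work without the time of cessation, so the death trigger needs no further timing item beyond the time of death. If the sponsor prefers to keep the narrower trigger, the article should say why death and NEC differ, and how a death soon after cessation reaches the DSMB between looks.

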## Discussion

AOP remains one of the most common diagnoses in preterm infants that can result in intermittent hypoxemia. It is important to protect infants from these periods of hypoxemia as they are associated with an increased risk for adverse long-term outcomes [2, 3]. Doxapram is frequently used off-label in some European countries as an add-on therapy to caffeine and non-invasive respiratory support, aiming to avoid invasive mechanical ventilation in the treatment of persisting apnoea. However, sufficient evidence on the safety and efficacy of doxapram is lacking. Concerns of impact on cerebral function and brain development may hamper the healthy development of doxapram-treated premature infants [18, 19]. Previously, a comparable placebo-controlled trial with caffeine therapy was conducted, resulting in a reduced rate of BPD and an improved rate of survival without neurodevelopmental disability in the caffeine group [4, 48]. Doxapram has the potential to improve neonatal outcomes further [20], but the safety concerns need to be weighed against these potential benefits and the suspected risks of invasive mechanical ventilation. Which of these two is best on the long-term is unknown and forms the clinical equipoise of the current trial. This international, multicentre trial will provide the needed high-quality evidence on the efficacy and safety of doxapram in the treatment of AOP in preterm infants.

Doxapram is at present only registered in children ≥12 years and adults for the treatment of post anaesthetic respiratory depression, where its use is very limited [49]. It is however also suggested to be effective in reducing the number of apnoea and desaturations in preterm infants [8, 9, 50], although this effect is not observed in every infant treated with doxapram [51]. Decades ago, small randomized controlled trials compared doxapram with either placebo or theophylline without evaluating the long-term effects [52–55]. An observational study found a higher cumulative doxapram dosage in preterm infants with neurodevelopmental impairment compared to matched controls with a normal mental development, although this association could be confounded by indication [56]. Another observational study found no increased risk of the combined outcome death or neurodevelopmental delay, and even suggests a positive effect of doxapram [20]. Participants of the trial will be closely monitored, as no firm conclusions on efficacy and safety can be drawn.

A limitation of this trial is that the potential direct respiratory effect of the study medication cannot be blinded, although the assessor of the primary outcome will be blinded for the allocated treatment arm. Another challenge is the absence of uniform criteria to evaluate when the frequency and duration of apnoea are considered unacceptable and an intervention is needed. Poets et al. developed an interesting apnoea score to assess the severity of apnoea, but this score is not validated yet and is mostly a reflection of current clinical practice [57]. The rate of apnoea and hypoxic events can also fluctuate largely within and between patients, and detection can be difficult [51, 58]. We therefore chose for a more pragmatic design with less strict inclusion criteria. The decisions to start doxapram in routine clinical care, to adjust its dosage, or to stop doxapram therapy are made by the attending physicians. Enrolment of a participant in the study is done according to the existing clinical protocols and can vary between centres and physicians, as does the dosing and duration of study drug therapy. This pragmatic strategy was chosen to make the trial clinically feasible, relevant and to increase generalizability to other centres. Randomization of participants is stratified per centre, and we will adjust for this stratification in the analysis. The respiratory status before starting doxapram will be evaluated in a subset of the participants using continuous monitoring data. With these data, we aim to find more objective parameters and criteria for the indication to start doxapram therapy in future patients.

This trial will provide knowledge to improve the optimal treatment of preterm infants suffering from AOP. We will evaluate the safety and efficacy of doxapram in reducing death and severe disability in the first years of life. If doxapram is safe and effective, the treatment could be implemented in more NICUs worldwide. The placebo design may also provide the opportunity to identify patients who will benefit from doxapram therapy and those who will not. Evaluation of the exposure to doxapram and keto-doxapram will enable us to optimize dosing in future individual patients. An improved, more individualized AOP treatment policy will likely prevent patients from periods of hypoxemia and unnecessary treatment risks. Overall, this randomized, placebo-controlled trial aims to improve long-term patient outcomes.

